### Potential risks and benefits

Children in the STARS trial will be exposed only to synthetic and biologic disease modifying antirheumatic drugs (DMARDs) that had been licensed for use in JIA. Children in Step-up arm will be formally treated in accordance with current guidelines and drug licenses. Subjects in the Step-down arm will receive MTX (for less severe oligoarthritis patients) or etanercept (for polyarthritis and for more severe oligoarthritis patients) as a first-line treatment. Differently, in Europe, MTX is currently licensed only for use in polyarthritis and etanercept for polyarthritis when MTX has been demonstrated to be ineffective. However, around 70% of children with oligoarticular onset of JIA can expect to be prescribed MTX and around 50% of children with polyarthritis can expect to be prescribed etanercept throughout the course of their disease [15].

Treatment with MTX and etanercept is commonly believed to be associated with an increase of infection rate, in particular tuberculosis for etanercept. However, in a recent study with more than 8000 patients and 360,000 controls, the overall risk of acquiring an infection leading to hospital admittance was twofold higher in those with JIA than in those with attention deficit hyperactivity disorder [16]. This effect was already evident in patients with JIA not yet exposed to MTX or biologic agents and therefore is probably attributable to the immunological dysregulation associated with the chronic inflammatory disease. The risk of such infections was not further increased by use of MTX or etanercept. In contrast, treatment with high­dose glucocorticoids increased the infection risk by threefold. JIA itself confers risks for additional diseases, including autoimmunity and malignancies, especially lymphoma. In general, however, there is no direct evidence that an earlier introduction of these medications is associated with an increase of side effects frequency. In addition, MTX may a raise of liver enzymes; to minimise this risk, folinic acid is prescribed at one third to half the MTX dose the day after its administration. MTX can also cause severe nausea, thus anti-emetics are recommended as standard care. Other recommended measures in the trial to reduce risk from standard corticosteroid therapy include the use of proton pump inhibitors to minimise gastro-intestinal toxicity, and osteoporosis prophylaxis.

Treatment in both trial arms aims to reach a sustained and complete disease quiescence. The achievement of such state implies the disappearance of joint pain, morning stiffness and functional limitation. This objective may lead to restoration of the ability of the child to perform daily activities and to improve the quality of life of the child and the family. Sustained suppression of the inflammatory disease process may also help preventing long-term joint damage and, consequently, reduce the expenses of the health care system in terms of physiotherapy, need of devices (e.g. crutches, wheelchairs), orthopaedic surgery, etc. Another potential advantage of the therapeutic regimens assessed in the trial is avoiding disease exacerbations, which may require the prescription of systemic corticosteroids. Minimizing the use of these medications may lessen the frequency of serious adverse events secondary to their prolonged administration, particularly growth failure, weight gain, and cushingoid features. Sustained disease control may also reduce the need of repeated IACI, which cause distress to the child and the family and may increase the organizational and financial burden to the health care system in case general anaesthesia in the operatory theatre is needed. Broader objectives are the avoidance of absences of children from school and of parents from work, which may be caused by disease exacerbations or the request of frequent clinical visits or laboratory tests due to persistently active disease or continued treatment with potentially toxic medications. Particularly innovative aspects of the STARS trial include the use of standardised quantitative measures to assess the disease state and the disease course over time and the involvement of patients and parents in clinical decision making, through their assessment of disease activity by child-centred or patient-centred outcome measures.

## Methods

### Trial design

STARS is a 12-month multicentre randomised single-blinded superiority clinical trial of two different treatment strategies (Step-down versus Step-up) in a treat-to-target setting. After the conclusion of the observation period of the trial, patients will be followed for up to 5 years for the evaluation of the disease course, medication requirements, adverse events and long-term disease-related morbidity. Recruitment started on 21st May, 2019.

### Selection of centres

In a first phase, all Italian centres belonging to the Paediatric Rheumatology International Trials Organization (PRINTO) were invited to participate in the study. In January 2022, after a feasibility survey, PRINTO centers outside Italy were also invited to participate, based on the possibility to prescribe MTX in oligoarthritis and etanercept in polyarthritis as a first-line treatment according to local rules.

### Study population

Recent-onset JIA patients with oligoarthritis or rheumatoid factor negative polyarthritis aged between 2 and 17 will be included in the study. Participants must be DMARD-naïve (only treatment with one NSAID is allowed for no more than 6 weeks from diagnosis) and must not have received corticosteroid joint injections in the 3 months before enrolment.

After obtaining written consents (and assent where appropriate) from the participant, parent or legal guardian, patients’ disease severity will be assessed based on the clinical phenotype (irrespective of the ILAR classification) and the severity of the disease. Disease severity will be defined according to the extension of arthritis and based on the presence/absence of features of poor prognosis according to the 2011 American College of Rheumatology (ACR) recommendations for the treatment of JIA [2] (Table 1). Children with oligoarthritis without features of poor prognosis will be considered as “less severe patients”, children with RF-negative arthritis and children with oligoarthritis and features of poor prognosis will be considered as “more severe patients”. As stated in the 2011 recommendations, risk stratification is crucial for guiding optimal treatment; features of poor prognosis for oligoarthritis were defined by the recommendations panel based both on literature revision and on the panellists’ clinical experience [2]. In particular, the possible role of erythrocyte sedimentation rate as a predictor of a less favourable outcome for oligoarthritis patients was more recently confirmed by the results of a clinical trial on this subgroup of patients [17].

**Table 1 Tab1:** Subjects in both arms are grouped according to the severity of the disease, based on the 2011 American College of Rheumatology recommendations for the treatment of juvenile idiopathic arthritis (ref. [2])

**More severe patients**	
- Children with RF negative polyarthritis	
- Children with oligoarthritis AND features of poor prognosis:	
a. Arthritis of the hip or cervical spine	
b. Arthritis of the ankle or wrist and marked (> 40 mm/h) or prolonged (> 20 in at least 3 consecutive assessments within 3 months) erythrocyte sedimentation rate elevation	
**Less severe patients**	
- Children with oligoarthritis WITHOUT features of poor prognosis	

### Interventions

After the screening visit and recording of informed consent, patients will be randomised into two treatment arms: “Step-up” and “Step-down”. Patients in the Step-up arm will be treated according to a conventional strategy based on treatment escalation and driven by the treat-to-target strategy. Patients in the Step-down arm will be treated with an early, combined, aggressive therapy for 6 months.

In the Step-up arm, less severe patients will receive IACI in all affected joints without systemic therapies. If the juvenile arthritis disease activity score-10 (JADAS10) state of minimal disease activity (MiDA) after 3 months or the JADAS10 inactive disease (ID) state at 6 months are not reached, treatment with MTX will be started preferably subcutaneously in a single weekly dose of 15 mg/m2 (max 20 mg) and IACI can be repeated. Then, if the states of JADAS MiDA after 3 months or JADAS ID at 6 months are not reached, treatment with an anti-TNF agent in a single weekly dose of 0.8 mg/kg (max 50 mg) subcutaneously will be started. More severe patients in Step-up arm will receive IACI(s) and MTX as a first step and then escalate therapy with the same pathway, adding an anti-TNF treatment as a second step and switching to a different biologic medication as a third step (Fig. 1).

**Fig. 1 Fig1:**
[figure not shown]
Step-up arm design. T2T Group 1: Subjects with oligoarthritis without features of poor prognosis. T2T Group 2: Subjects with oligoarthritis with features of poor prognosis and subjects with polyarthritis. JADAS: Juvenile Arthritis Disease Activity Score-10. JADAS< 50%: improvement of JADAS10 of at least 50%, JADAS<ID: JADAS10 score below inactive disease cutoff. JADAS<HDA: JADAS10 score under HDA cutoffs. JADAS>HDA: JADAS10 score above HDA cutoffs. If at the visit 3 months after step 1, 2, and 3 the patient is improved by less than 50% in the JADAS score, but he/she reaches the JADAS state of minimal disease activity, treatment is not escalated ID = inactive disease, HDA = high disease activity. CR on med.: clinical remission on medication. IACI: intra-articular corticosteroids injection. +MTX: start methotrexate (repeating IACI or adding a short course of prednisone can be considered). +TNF: add therapy with an anti-TNF agent (repeating IACI or adding a short course of prednisone can be considered). +TNF2: replace anti-TNF agent with another an anti-TNF agent or with an anti IL-6 agent (repeating IACI or adding a short course of prednisone can be considered)

Patients allocated to the Step-down arm (Fig. 2) will receive an early combined treatment (MTX plus IACI for less severe oligoarthritis, MTX plus etanercept for severe oligoarthritis and polyarthritis). After 6 months, if JADAS10 ID is achieved, less severe patients will have MTX discontinued, whereas more severe patients will stop etanercept and continue MTX. Children in Step-down arm experiencing a worsening from the baseline of the JADAS10 at 3 months, not achieving JADAS10 ID at month 6, or losing the state of ID after month 6 will be considered as treatment failures and will change treatment according to the attending physician decision.

**Fig. 2 Fig2:**

Step-down arm design. Step A is start methotrexate plus intra-articular joint injections for oligoarthritis without features of poor prognosis, methotrexate plus etanercept and optional intra-articular joint injections for other patients. Step B is withdraw methotrexate for oligoarthritis without features of poor prognosis, withdraw etanercept and continue methotrexate for other patients. JADAS: Juvenile Arthritis Disease Activity Score-10. JADAS<ID: JADAS10 score below inactive disease cutoff. CR on med.: clinical remission on medication

For the IACIs, triamcinolone hexacetonide will be administered at a dose of 1 mg/kg (max 40 mg) in the hips, knees and shoulders, at the dose of 0.75 mg/kg (max 30 mg) in the ankles and elbows, at the dose of 0.5 mg/kg (max 20 mg) in the wrists; methylprednisolone acetate will be administered at the dose of 1 mg/kg (max 40 mg) in the subtalar and inter-tarsal joints and at the dose of 5–10 mg, depending on the size of the child, in the small joints of hands and feet. A course of oral prednisone instead of or in addition to joint injection can be prescribed in case hip, temporomandibular joints or cervical spine are involved, or in case more than four joints are affected or joint injections cannot be performed.

### Patients’ assessment and disease activity monitoring

Complete physical examination with joints assessment, main patient/parent reported outcomes collection (including pain level, morning stiffness duration, disease activity self-assessment, physical function, and health-related quality of life), uveitis screening, medication history, treatment adverse events evaluation, and laboratory tests (haematological and biochemical analysis and urinalysis) will be performed at each trial visit.

The level and state of disease activity will be measured in all patients at each step of the study by means of the JADAS10. The JADAS10 [18] is a composite disease activity score validate for use in children with JIA and includes the following 4 measures: physician’s global assessment of disease activity, measured on a 0–10 21-circle Visual Analogue Scale (VAS) where 0 = no activity and 10 = maximum activity; parent/patient global assessment of well-being, measured on a 0–10 21-circle VAS where 0 = very well and 10 = very poor; the count of joints with active disease cut at 10 joints (i.e. 1 point for each active joint up to a maximum of 10 points); and the erythrocyte sedimentation rate (ESR), normalised to a 0 to 10 scale according to the following formula: (ESR (mm/hour) – 20)/10. Before making the calculation, ESR values < 20 mm/hour are converted to 20 and ESR values > 120 m/hour are converted to 120. The definition of the disease states of ID, MiDA, and high disease activity (HDA) based on the JADAS10 refers to the newest version of JADAS10 cut-off values [19, 20]. New cutoffs for oligoarthritis and polyarthritis are shown in Table 2. Data will be collected electronically in the PRINTO web-based platform designed for the PharmaChild registry.

**Table 2 Tab2:** New JADAS10 and cJADAS10 cutoffs for disease activity states (Refs [16, 17])

	JADAS10	cJADAS10
**Oligoarthritis**		
Inactive disease	≤1.4	≤1.1
Minimal disease activity	1.5–4	1.2–4
Moderate disease activity	4.1–13	4.1–12
High disease activity	> 13	> 12
**Polyarthritis**		
Inactive disease	≤2.7	≤2.5
Minimal disease activity	2.7–6	2.5–5
Moderate disease activity	6.1–17	5.1–16
High disease activity	> 17	> 16

### Endpoints

The effectiveness of the two therapeutic strategies will be compared by assessing the frequency of clinical remission (CR) at 12 months [21]. CR is defined as the persistence of the JADAS10 state of ID for at least 6 months. Patients will be considered to be in ID from the day of the first visit with JADAS10 ID until the day before the first subsequent visit in which the patient is found to have lost the state of JADAS10 ID. Then, a number of secondary endpoints will be assessed in order to better understand the efficacy of the two treatment strategies (Table 3). The rate of patients achieving the JADAS-defined and the ACR-defined state of ID, the time to achieve ID and clinical remission, the time spent in inactive disease, the cumulative level of disease activity and the rate of uveitis will be compared between the two arms.

**Table 3 Tab3:** STARS trial endpoints

**Primary endpoint**	
Clinical remission on or off medication at 12 months.	
The effectiveness of the two therapeutic strategies will be compared by assessing the frequency of clinical remission (CR) at 12 months. CR is defined as the persistence of the JADAS state of ID for at least 6 months	
**Secondary endpoints**	
Inactive disease	
The rate of patients who achieve the JADAS/JIA ACR state of ID at any single point in time throughout the study period will be compared between the 2 arms.	
Time to inactive disease as per JADAS/JIA ACR criteria	
Time to achieve the JADAS/JIA ACR state of ID will be calculated as the time difference (in days) between the date of randomization and the date of the visit on which the patient will be observed to be in ID.	
Time to JADAS/JIA ACR clinical remission	
Time to achieve the JADAS/JIA ACR state of clinical remission will be calculated as the time difference (in days) between the date of randomization and the date of the visit on which the patient will be observed to be in clinical remission (i.e. persistent inactive disease for at least 6 months).	
Time spent in JADAS/JIA ACR inactive disease	
The cumulative time spent in the JADAS/JIA ACR state of ID will be calculated as the time difference (in days) between the date of the first visit on which the patient will be observed to be in ID and the date on which he/she will be observed to be no longer in ID, that is when the disease will flare (see later for definitions), or database closure for analysis purposes. We will assume that if a patient is found to be in ID at 2 consecutive visits, the patient had ID on all days between these visits. If a patient will be found to have ID at a particular visit, but lost the ID status at the subsequent visit, the patient will be considered to have been in ID until the recurrence of active disease. Patients found to be in ID only at the time of database closure will contribute a single day of ID. The time in inactive disease per patient will be recorded and compared between the 2 arms.	
Cumulative level of disease activity throughout the study period	
The area under the curve of the JADAS10 score assessed at every study visit and the AUC of the parent version of the JADAS (parJADAS) assessed monthly will be recorded and compared between the 2 arms.	
Time spent on therapy	
The cumulative time on therapy will be calculated as the time difference (in days) between the date of the visit on which the patient will start a systemic medication (synthetic or biologic DMARDs or steroids) and the date on which he/she will be observed to no longer be in treatment with a systemic medication or completed the study. We assume that if a patient does not receive medications at 2 consecutive visits, the patient had not received medications everyday between these visits. Patients initiating a systemic treatment at the final visit of the study will contribute a single day of time in therapy. The mean percentage of time spent on therapy per patient will be recorded and compared between the 2 arms.	
Rate of flares	
The rate of patients who develop flare, defined as the recurrence of active disease after attaining inactive disease at last visit according to JADAS or JIA ACR definition, and the number of flares and the time to flare per patient will be recorded and compared. Notably, all patients prescribed intra-articular injections, synthetic or biologic DMARDs or systemic steroids will be considered as flare independently from JADAS or ACR criteria.	
Rate of uveitis onset	
The rate of patients who develop uveitis according to the Standardized Uveitis Nomenclature (SUN) will be recorded and compared between the 2 arms. The rate of patients requiring systemic medications for treatment of uveitis will be also recorded and compared between the 2 arms. However, these patients will be excluded from the study and followed for safety only.	

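### Time in inactive disease is labelled cumulative but defined as one interval ending at loss of inactive disease or database closure, which omits regained spells and sets no 12-month limit

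*Protocol article*

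**What the plan says.** The definition is in Table 3 of the protocol article, under the secondary endpoint on time spent in inactive disease. Label and formula share one sentence, which begins "The cumulative time spent in the JADAS/JIA ACR state of ID will be calculated as the time difference (in days". The interval runs between "the date of the first visit on which the patient will be observed to be in ID and the date on which" the child is found to have lost ID, which the text equates with flare. For a child who does not flare, the end is "or database closure for analysis purposes". A further rule says: "Patients found to be in ID only at the time of database closure will contribute a single day of ID". The comparison is then stated as "The time in inactive disease per patient will be recorded and compared between the 2 arms", with no follow-up denominator.

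Three other places bear on this:

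- **Time spent on therapy (Table 3).** This companion endpoint ends when systemic treatment stops or the child completes the study, and it is compared as a percentage: "The mean percentage of time spent on therapy per patient will be recorded and compared between the 2 arms".
- **Rate of flares (Table 3).** The number of flares per patient is recorded and compared, so the plan expects some children to lose ID more than once.
- **Trial design.** "STARS is a 12-month multicentre randomised single-blinded superiority clinical trial", after which children are followed for up to 5 years. Recruitment began on 21 May 2019. Selection of centres adds that centres outside Italy were invited in January 2022. Trial status reports 113 children recruited, against the 260 planned under Sample size.

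**The concern.** The formula does not match its label in two respects.

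First, a single difference that starts at the first ID visit and stops at the first loss of ID gives no credit for ID regained later. Regaining ID is foreseeable in both arms. Step-up escalates in stages when the target is missed, and Step-down children who lose ID after month 6 change treatment. A measure meant to show how long each strategy keeps children in ID would, read literally, report only the length of the first spell.

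Second, database closure is a calendar date, whereas the trial period is 12 months from each child's entry. Entry is staggered over years and follow-up continues after month 12. If closure is later than a child's 12-month visit and the later data are in the closed database, two children with the same 12-month course receive different scores because they enrolled at different times.

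At stake is the interpretation of one secondary endpoint: whether its result can be read as days in ID over the 12-month trial.

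**Working it through.** **The plan's own figures.** The article gives no number for this endpoint, so there is none to reproduce. The sample size is not an input here. For the record, it does reproduce: 0.45 versus 0.25, two-sided 0.05, power 0.8, with continuity correction gives 98 per arm, and 98 / 0.9 = 108.9, rounded up to the stated 109.

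**Assumptions.** The article does not give the full visit schedule or the closure date. I assume visits at days 91, 183, 274 and 365 (months 3, 6, 9 and 12), and closure at day 365 or day 730 after a child's entry.

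**Formulas.**

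- Literal rule: (date of first visit out of ID after the first ID visit, or closure if there is none) minus (date of first ID visit). The value is 1 day if ID is first seen at closure.
- Summed rule: for each visit in ID, add the days to the next visit, stopping at day 365. Add 1 day if ID is newly seen at day 365.

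**Check 1: regained spells, closure at day 365.** Four visits give 16 possible ID patterns. In five of them ID is lost and regained:

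| In ID at months | Literal rule (days) | Summed rule (days) | Dropped (days) |
|---|---|---|---|
| 3, 9, 12 | 183 − 91 = 92 | 92 + (365 − 274) = 183 | 91 |
| 3, 9 | 183 − 91 = 92 | 92 + (365 − 274) = 183 | 91 |
| 3, 12 | 183 − 91 = 92 | 92 + 1 = 93 | 1 |
| 6, 12 | 274 − 183 = 91 | 91 + 1 = 92 | 1 |
| 3, 6, 12 | 274 − 91 = 183 | 183 + 1 = 184 | 1 |

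In the other 11 patterns the two rules agree. Within 12 months the dropped time is therefore at most 91 days per child, which is half of 183. It is only 1 day where ID is regained at the last visit.

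**Check 2: closure date, literal rule, ID not lost again.**

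| First in ID at | Closure at day 365 | Closure at day 730 |
|---|---|---|
| Month 3 | 365 − 91 = 274 | 730 − 91 = 639 |
| Month 6 | 365 − 183 = 182 | 730 − 183 = 547 |
| Month 12 | 1 | 730 − 365 = 365 |

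For a child in ID from month 3 the ratio is 639 / 274 = 2.3 with the same disease course over the trial year. Each extra day to closure adds one day, but only for children whose first spell is still unbroken.

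**How far apart entry dates can be.** From 21 May 2019 to 1 January 2022, the start of the month in which centres outside Italy were invited, is 956 days. The longest spell available from month 3 to month 12 is 274 days. The room for unequal follow-up is therefore large if closure is one calendar date and post-month-12 data count.

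**Under the summed rule cut at month 12.** The child in ID at months 3, 9 and 12 scores 183 / 365 = 50% of the year. The child in ID at all four visits scores 274 / 365 = 75%, whatever the enrolment date.

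**The case against.** The strongest reply is that the text is loosely worded and the intention is sound. The word cumulative points to adding spells. The rules for pairs of visits are general and not limited to the first spell, so the sentence with the time difference may describe one spell among several. Time on therapy is also called cumulative and also written as one difference. Closure for analysis purposes may mean a data cut at 12 months: ID can only be found at a visit, and the single-day rule resembles the rule for treatment started at the final visit under time on therapy. All of this is plausible, and it is why the point is limited to what the text says when followed literally. It does not remove the problem. No sentence restarts the clock, adds a second spell or names the 12-month visit as the end.

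A reader might infer more than the document supports in three ways:

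- **That one arm is favoured.** Either arm can lose and regain ID, and randomisation should balance entry dates. Unequal closure mainly adds noise and changes what is measured. No direction of bias is shown.
- **That several years of extra ID are certain to be counted.** This requires the long-term follow-up to be pooled into this endpoint. The article places that follow-up after the trial's observation period and does not say that it is pooled.
- **That the area-under-the-curve endpoint shares the defect.** Its text, "The area under the curve of the JADAS10 score assessed at every study visit", has neither a first-spell rule nor a closure date, and its title sets the window as the study period. How early leavers enter it is missing-data detail normally left to the full protocol or analysis plan.

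**Conclusion.** The point holds as a mis-specified secondary endpoint. Followed literally, the definition omits regained ID, which contradicts its own label and the counting of several flares per child. It also lets children still in ID accrue days beyond month 12 if closure comes later than that visit.

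With assumed 3-monthly visits, the omission costs a child up to 91 of 183 days within the trial year, and usually much less or nothing. With an assumed closure at 24 months instead of 12, a child in unbroken ID from month 3 scores 639 days instead of 274. How many children would be affected cannot be worked out from the article.

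The consequence is an unclear estimand and added noise. The primary endpoint and sample size do not depend on this definition.

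**What to change.** Redefine the endpoint, in both its JADAS and ACR versions, as the sum of all ID spells from randomisation to the 12-month visit, or to the last visit before it for a child who leaves early. Express it as a percentage of the child's observed time in that window, the scale already used for time on therapy. Put the 12-month visit in place of database closure, including in the single-day rule. Report ID time after month 12 as a separate long-term description.

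The cost is wording and programming. No new data, visits or patients are needed. The change is best made before any comparison by arm is seen.

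### Time spent on therapy is dated by visit observation rather than recorded drug dates, so stops between visits are overcounted and the month-6 methotrexate stop can be read two ways (minor)

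*Protocol article*

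**What the plan says.** The definition is in Table 3 of the Protocol article, under the secondary endpoint on time spent on therapy.

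- Start of the clock: "the date of the visit on which the patient will start a systemic medication (synthetic or biologic DMARDs or steroids" (quote cut before the closing bracket).
- End of the clock: "the date on which he/she will be observed to no longer be in treatment with a systemic medication or completed the study".
- Between visits: "if a patient does not receive medications at 2 consecutive visits, the patient had not received medications everyday between these visits".
- Comparison: "The mean percentage of time spent on therapy per patient will be recorded and compared between the 2 arms".

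Three other places bear on it.

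- Methods, Interventions, on the Step-down arm: "After 6 months, if JADAS10 ID is achieved, less severe patients will have MTX discontinued". More severe Step-down children stop etanercept but continue methotrexate.
- Methods, on patients' assessment: the list of what is done at each trial visit includes "uveitis screening, medication history, treatment adverse events evaluation".
- Analysis plan: adverse-event rates by drug are to be estimated by dividing each child's follow-up into periods of drug administration.

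**The concern.** The wording closely follows that of the neighbouring endpoint on time in inactive disease. Visit dating is unavoidable there, because inactive disease is known only when the child is examined. Drug exposure is different: a start and a stop have dates that can be recorded whenever they occur. The safety analysis relies on administration periods, so the trial would measure exposure in two ways, and this endpoint would get the cruder one.

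The percentage of time on therapy is compared between arms, so an error that differs by arm would bias the comparison. The only planned withdrawal of all systemic drugs during the 12 months is in less severe Step-down children with inactive disease at month 6. If their stop is dated late, Step-down exposure is overstated, and the Step-up arm has no matching planned stop. The Rationale names a reduced need for later biologic agents among the trial's objectives, so drug exposure is of real interest.

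**Working it through.** The article gives no figure for time on therapy, so there is none to reproduce. The check applies the Table 3 rule to example courses and compares the result with actual dates.

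**Inputs**
- Trial length: 12 months (Trial design).
- Stated assessments: months 3 and 6 (Interventions). No month-9 visit appears in the text, and the figures are not available, so 3-monthly visits are an assumption.
- Less severe children: 57 of 113 recruited, both arms together (Trial status).
- One month = 30.44 days. Steroid course length is not given; 2 to 8 weeks is assumed.

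**1. Stop between visits.** A 3-month interval is 3 × 30.44 = 91 days. If the stop falls at a uniformly random time in the interval, the mean overcount is half of that, 91.3 / 2 = 46 days, or 1.5 / 12 = 12.5 percentage points for that child.

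**2. Methotrexate stopped at the month-6 visit.**

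| Reading | Months counted | Share of 12 months |
|---|---|---|
| Stop counts as observed at month 6 | 6 (183 days) | 50% |
| Observed at next visit, month 9 (assumed) | 9 (274 days) | 75% |
| Observed at next visit, if visits are monthly | 7 (213 days) | 58% |
| Observed at next visit, if that is month 12 | 12 (365 days) | 100% |

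The first row equals the actual stop date, so there is no error. The second gives an excess of 75 − 50 = 25 points for that child.

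**3. Effect on the Step-down mean under the month-9 reading.** Less severe share: 57 / 113 = 0.504, assumed equal in the two arms. Assume that 25% to 75% of these children stop at month 6 and are still off drug at the next visit:

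- 0.504 × 0.25 × 25 = 3.2 points
- 0.504 × 0.75 × 25 = 9.5 points

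The shift is thus roughly 3 to 9 points, and scales in proportion to the excess per child.

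**4. Short steroid courses with no DMARD running.** Courses of 2, 4 and 8 weeks are 14, 28 and 56 days: 14 / 365.25 = 3.8%, 28 / 365.25 = 7.7% and 56 / 365.25 = 15.3% of the year.

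- Started at a visit and over by the next: counted as about 91 days (25%), which is 6.5, 3.3 and 1.6 times the true length.
- Begun and ended between two off-drug visits: counted as 0 days.

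Where a DMARD runs throughout, the day is already counted and the steroid course changes nothing.

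**The case against.** **The methotrexate figure is not fixed by the text.** A reader might infer that a 6-month course will be recorded as 9 months. The start of the clock is tied to a visit date, but the end is tied only to the date of observation. Table 3 also credits one day to a child who starts treatment at the final visit, so a change ordered at a visit seems to count from that visit. By the same logic a stop ordered at month 6 is observed at month 6, and the error is nil. This stands in part: no error is a fair reading. The other reading is also fair, because the Endpoints section ends inactive disease only when a later visit finds it lost, and Table 3 words the end of therapy in a similar way. The text does not decide between them.

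**The steroid problem is narrow.** A reader might infer that steroids are a main early exposure of less severe Step-up children. The documents do not support that. In the Fig. 1 legend, "adding a short course of prednisone can be considered" belongs to steps at which methotrexate or a biologic is started or replaced. Interventions says that less severe Step-up children begin without systemic treatment. Of the situations listed there for oral prednisone, hip or cervical spine disease places a child in the more severe group under Table 1, and more than four affected joints would ordinarily do so too. Those children receive methotrexate from the start in both arms. Temporomandibular disease and injections that cannot be performed remain, with no frequency given. This objection largely stands.

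**Stop dates may not all be captured, and date derivation often belongs in the analysis plan.** The article mentions medication history without naming stop dates, and it does not say that the diary cards cover prednisone. That is fair, and the fix includes a check. But the article does more than leave the derivation open: it states a visit-based rule, and that rule can be reviewed.

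**Conclusion.** The point holds as a minor one. The rule dates exposure by observation, and the assumption about two off-drug visits confirms it. Three consequences follow:

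- A systemic drug stopped between visits is overcounted, by about 46 days on average if visits are 3-monthly and stops fall at random between them.
- A systemic course that lies wholly between two off-drug visits is missed. This matters only when no DMARD is running, so probably in few children.
- The month-6 methotrexate stop can be counted as 6 months or up to the next visit, which is 9 months if a month-9 visit exists.

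It would be wrong to conclude that the arm comparison is biased by 25 points. That is the excess for a single child, on one of two readings and with an unstated visit. The corresponding shift in the Step-down mean is roughly 3 to 9 points, under the assumed 25% to 75% who stop and an equal severity mix in the arms; on the other reading it is zero. The primary endpoint, the sample size and the safety exposure method are not affected.

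**What to change.** Define time on therapy as the number of days from randomisation to month 12 covered by at least one systemic drug, taken from recorded start and stop dates, with overlapping drugs counted once. Express it as a percentage of that period. This agrees with the administration periods already planned for the safety analysis. Keep the visit-based assumption only for a missing date, and state that a stop ordered at a visit takes that visit's date unless another is recorded.

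The cost is small: rewording one secondary endpoint, date-based programming, and a check that start and stop dates are captured for steroids as well as DMARDs. Treatment and visits do not change.
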